### 2.8. Chuna Manual Therapy (CMT)

The CMT regimen for cervicogenic dizziness has been determined based on a textbook for Chuna manual medicine [24], several previous CMT studies for neck pain [25–29], and experts' opinions. Since this pragmatic study was designed to reflect clinical settings, the CMT techniques are individualized depending on each patient's condition. We also referred to a lower back pain study with similar CMT performance [16]. The final regimen was externally reviewed by the Korean Society of Chuna Manual Medicine for Spine & Nerve (http://www.chuna.or.kr), and the feasibility of the approach for cervicogenic dizziness was confirmed.

The CMT techniques in this study consist of mandatory and discretionary parts. The mandatory techniques are flexion distraction and dysfunction correction for the cervical spine, while the discretionary techniques apply to other regions (thoracic or lumbar parts). Only TKM doctors who have completed the regular CMT curriculum and have had 1 year or more of experience in clinical practice will be qualified as CMT practitioners for this study. The practitioners will assess the patients before each session and decide which discretionary techniques are necessary for each patient. The techniques applied will be reported for every session, using case report forms. The detailed CMT regimen is shown in Table 2. The procedures that will be followed are derived from an accredited textbook [24].

Participants who are allocated to the CMT group will receive 12 sessions of CMT over 6 weeks (2 sessions/week).

### 2.9. Usual Care (UC)

No standard therapy for cervicogenic dizziness has been determined yet. A review study suggested that cervicogenic dizziness should be managed in the same way as neck pain [3]. Therefore, we have decided to educate the patients and allow both groups to have TKM-based physical therapies for neck symptoms, based on previous studies [3, 5, 8, 10] and clinical opinions. For the purposes of this study, these treatments are designated as UC.

The patient education program will include (a) physical and pathological information concerning cervicogenic dizziness, (b) causes and risk factors for cervicogenic dizziness, (c) muscle functions related to cervicogenic dizziness, and (d) home exercising skills for management of cervicogenic dizziness. Physical therapy consists of electrical stimulation (either meridian muscle interferential current electricity or meridian transcutaneous electricity) and heat stimulation (either a heat pack or an infrared lamp) to relieve pain or stiffness in the neck muscles.

All participants who are allocated to the CMT or UC groups will receive 12 sessions of UC for 6 weeks (2 sessions/week).

### 2.10. Concomitant Medications

Drug administration (betahistine, difenidol, flunarizine, cinnarizine, dimenhydrinate, ginko, meclizine, metoclopramide, scopolamine, pentoxifylline, perphenazine, ergoloid mesylate, droperidol, phenobarbital, prochlorperazine, promethazine, trimethobenzamide, vertigoheel, NSAIDs, steroids, etc.), herbal remedies, manual therapies, any type of acupuncture, moxibustion, or cupping, to relieve dizziness, back pain, or stiffness, will be forbidden throughout the study.

Any signs of the use of drugs that can induce dizziness will be monitored closely during every visit.

### 2.11. Screening Process

After informed consent is obtained, each patient will undergo a screening process for eligibility assessment. Demographic information (initial of name, age, and sex), physical examination results (height, weight, and body mass index), vital signs (blood pressure, pulse, and body temperature), and pregnancy test results (if available) will be collected. The medical history (past and present) and concomitant medications or therapies will be investigated. To exclude other types of dizziness, we will also administer tests of CNS function (deep tendon reflex, Hoffman sign, Babinski sign, ankle clonus, finger-to-nose, finger-to-finger, rapid alternating movement, heel-to-shin, Romberg's test, Brudzinski's sign, Kernig's sign, Naffziger's test, and Gorge's test) and nystagmus tests (spontaneous, gaze-evoked, positional, and positioning (Dix-Hallpike) nystagmus tests). If a patient does not seem to have any other identifiable cause of dizziness, the final decision on eligibility will be made by a TKM doctor.

### 2.12. Outcomes

#### 2.12.1. Primary Outcome

*Dizziness Handicap Inventory (DHI). *The DHI is a patient-rated outcome (PRO) assessment that evaluates dizziness-induced impairments functionally, emotionally, and physically [30]. A Korean version of the scale has been validated [31]. The scale, consisting of 25 items with 4 points for each (scores 0–100), is frequently used for cervicogenic dizziness [2, 10–13]. The primary endpoint is defined as the mean difference of DHI total scores between day 0 and week 6. Subordinately, the intergroup effect at an intermediate time point (the mean difference between day 0 and week 3), as well as intragroup effects within each group, will be analyzed.

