### 2.2. Study Design

This study is a prospective, pragmatic, assessor-blind, randomized controlled trial. Fifty patients complaining of recurring dizziness with cervical origins, with DHI score ≥ 16 at baseline, will be randomly allocated to either the CMT or UC group, with a 1 : 1 ratio. After eligibility assessment and a 1-week run-in period, the participants will receive 12 sessions of CMT combined with UC, or UC only, over 6 weeks. CMT consists of mandatory and discretionary techniques, and skilled KMD doctors will perform the techniques considered to be optimal for each patient's condition. This latitude in treatment selection is why the study is designated as pragmatic. UC includes electrotherapy, thermotherapy, and patient education. A flowchart and timetable for the study are shown in Figure 1 and Table 1, respectively.

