### 2.15. Sample Size Calculation

RCTs evaluating the efficacy of a manual therapy, compared with placebo, for cervicogenic dizziness gave values for the mean changes and standard deviations [11, 13]. With 15.9 as the mean difference between the intervention and control groups and 12.91 as the standard deviation, the necessary sample size calculated using PASS 14 was 12 per group (two-sided, *α* = 0.05 and 1 − *β* = 0.9). We will allocate a total of 50 participants (25 per group), allowing for an anticipated drop-out rate of 40%.

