### 2.16. Statistical Analysis

The full analysis set is defined as the group of participants who received CMT or UC and were assessed for the primary outcome at least once. The “per protocol” set is defined as the group of participants who completed all planned interventions and outcome assessments. Efficacy data will be analyzed primarily using the full analysis set and secondarily using the per protocol set. The missing data will be imputed using the “last observation carried forward” method. Safety data will be analyzed using the safety assessment set, which is defined as the group of participants who received CMT or UC at least once.

The primary and secondary outcomes will be statistically analyzed using two-sample *t*-tests or Wilcoxon's rank-sum tests for intergroup comparisons and paired *t*-tests or Wilcoxon's signed-rank tests for intragroup comparisons. Categorical variables from demographic data or AEs will be analyzed using the Chi-square test or Fisher's exact test.

An independent statistician ([name]) will analyze the data at *p* < 0.05 with SAS 9.4 software (SAS Institute Inc.).

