**Enrollment:**										
*Informed consent*	×									
*Demographics *	×									
*Physical examination*	×									
*Vital signs*	×									
*Pregnancy test*	×									
*Medical history*	×									
*Concomitant medication*	×	×	×	×	×	×	×	×	×	×
*CNS examination*	×									
*Nystagmus examination*	×									
*Eligibility assessment*	×									
*Random allocation*		×								

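### The primary DHI comparison adjusts for no baseline score, although the DHI is measured twice before treatment; a baseline-adjusted model would usually be more precise on data already collected

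*Protocol article*

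**What the plan says.** Table 1 of the protocol article schedules the DHI at V1 (−1 week), V2 (day 0), V7 (week 3) and V13 (week 6). V1 and V2 both precede treatment.

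Section 2.12.1 fixes the endpoint: "The primary endpoint is defined as the mean difference of DHI total scores between day 0 and week 6". Section 2.16 fixes the test for primary and secondary outcomes: "two-sample *t*-tests or Wilcoxon's rank-sum tests for intergroup comparisons". Neither test takes a covariate.

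V1 has an apparent use. Section 2.5 requires DHI ≥ 16 at baseline without naming the visit. Table 1 marks "Eligibility assessment" at V1 only, and section 2.2 says treatment starts "After eligibility assessment and a 1-week run-in period".

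On size, section 2.15 works "With 15.9 as the mean difference between the intervention and control groups and 12.91 as the standard deviation", and enrols 25 per group against 40% drop-out.

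**The concern.** A change score subtracts the whole of the day-0 score. That is optimal only if a one-point difference at baseline carries through as one point at week 6. When the baseline-to-week-6 correlation is below 1 and the variances are similar, subtracting too much adds noise. ANCOVA estimates the right amount to subtract and estimates the same treatment effect with a smaller standard error.

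The trial also holds a second pre-treatment DHI reading, which could sharpen the adjustment further. The stated tests can use neither score in this way. With perhaps 30 completers, wider confidence intervals on the primary outcome matter, and the data to narrow them are already scheduled.

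**Working it through.** **The plan's own figures.** Section 2.15 gives a difference of 15.9, SD 12.91, two-sided α 0.05 and power 0.90. The normal approximation gives 2 × (1.960 + 1.282)² × (12.91/15.9)² = 13.9, so 14 per group. The exact t-test needs 15. The printed 12 is not reproduced: it gives 82.2% power. The enrolled 25 per group does fit 15, since 15/0.6 = 25, and 15 completers per group give 90.2%. The mismatch over 12 is a separate matter. Here the useful figure is 25 × 0.6 = 15 completers per group, 30 in all.

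**Inputs that are assumed.** The documents give no DHI correlations. Write r01 for V1–V2, r2 for V2–week 6 and r1 for V1–week 6. I take r01 from 0.6 to 0.9 and r2 and r1 from 0.5 to 0.7, with equal variances at all three times (set to 1).

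**Formulas.**
- Planned change score: 2(1 − r2)
- ANCOVA on day 0: 1 − r2²
- ANCOVA on the mean of V1 and V2: 1 − [(r1 + r2)/2]² / [(1 + r01)/2]
- ANCOVA on V1 and V2: 1 − (r1² + r2² − 2·r1·r2·r01)/(1 − r01²)

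Estimating covariate slopes has a small-sample cost. Relative to the unadjusted test, the expected variance of the treatment estimate is multiplied by (n − 3)/(n − 4) for one covariate and (n − 3)/(n − 5) for two. At n = 30 these are 27/26 = 1.038 and 27/25 = 1.080. The second covariate alone costs 26/25 = 1.04 at n = 30 and 46/45 = 1.022 at n = 50.

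**One case in full** (r01 = 0.8, r2 = r1 = 0.6). Change score: 2 × 0.4 = 0.80. Day-0 ANCOVA: 1 − 0.36 = 0.64, ratio 0.80; times 1.038 this is 0.831, a 16.9% cut. Mean of both: 1 − 0.36/0.90 = 0.60, ratio 0.75; times 1.038 this is 0.779, a 22.1% cut. Both as covariates: the same 0.75, times 1.080 this is 0.81, a 19.0% cut.

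**Variance cut against the planned test, n = 30, small-sample cost included:**

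| r01 / r2 / r1 | Day 0 only | Mean of V1, V2 | V1 and V2 |
|---|---|---|---|
| 0.6 / 0.6 / 0.6 | 16.9% | 28.6% | 25.8% |
| 0.6 / 0.5 / 0.5 | 22.1% | 28.6% | 25.8% |
| 0.8 / 0.6 / 0.6 | 16.9% | 22.1% | 19.0% |
| 0.9 / 0.7 / 0.7 | 11.7% | 16.2% | 12.8% |
| 0.8 / 0.6 / 0.5 | 16.9% | 13.8% | 13.8% |
| 0.9 / 0.6 / 0.5 | 16.9% | 11.5% | 14.7% |
| 0.8 / 0.7 / 0.6 | 11.7% | 8.2% | 9.0% |
| 0.8 / 0.7 / 0.5 | 11.7% | −3.8% | 10.0% |

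The first six rows give about 11–29%. The last two are less favourable: r2 is at the top of its range and V1 is the weaker predictor. Day-0 ANCOVA depends only on r2 and stays between 11.7% (r2 = 0.7) and 22.1% (r2 = 0.5).

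**V1's own increment.** Before the small-sample cost, V1 as a second covariate removes 14.1% beyond day-0 ANCOVA in the first row (0.688 against 0.800) and 0.2% in the fifth (0.799 against 0.800). After the 4% cost at n = 30 these become a 10.6% gain and a 3.8% loss. The top of this range is not a hard limit: with all three correlations at 0.7 the increment before cost is 17%.

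**The case against.** The strongest reply is that nothing here is wrong. A t-test on change from day 0 is unbiased under randomisation, and at the protocol's assumed effect 15 completers per group already give 90.2% power. V1 is a screening measure doing a screening job, and an unseen SAP could add adjusted analyses. Validity stands, and so does V1's apparent role in eligibility. The SAP argument stands only in part: the article does not leave the method open but names two tests that take no covariate.

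Three stronger readings are tempting and not supported.

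- A reader might infer that the planned comparison is biased or underpowered for want of V1. It is not biased, and the documents do not show a shortage of power at the stated effect.
- A reader might infer that V1 supplies cost-free precision as an independent second reading. It is a separate reading, but correlated with V2 and a week further from week 6. A second covariate has a real cost at this size.
- A reader might infer that the change should be taken from the average of V1 and V2. With correlations 0.8/0.6/0.5 that leaves the change-score variance unchanged, and with 0.9/0.6/0.5 it raises it by about 6%.

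It is also fair to say that most of the recoverable precision usually comes from the day-0 score. The point is therefore mainly about missing baseline adjustment and only secondarily about V1.

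**Conclusion.** The point holds as an efficiency recommendation of minor weight. Sections 2.12.1 and 2.16 fix an unadjusted comparison although two pre-treatment DHI scores are scheduled. Under the assumed correlations, ANCOVA lowers the variance of the primary comparison by about 11–29% at 30 completers, and by about 12–22% with day 0 alone. When day 0 correlates 0.7 with week 6 and V1 is clearly weaker, models that include V1 can fall below that band, and the averaged covariate can even do worse than the planned test. V1's own contribution is modest and may be nil or slightly negative after its small-sample cost.

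These figures rest on equal variances, linear relations and correlations that the documents do not give. They also take completers as the analysed sample. Section 2.16 carries the last observation forward, so the number analysed may lie nearer 50, where the small-sample cost is lower. Using V1 introduces no bias, because it precedes random allocation, even if entry was selected on it.

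**What to change.** In section 2.16, before outcome data are seen, replace the unadjusted test as the primary comparison with an ANCOVA of week-6 DHI on treatment and day-0 DHI. With day 0 as a covariate, modelling week 6 or the change from day 0 gives the same treatment estimate, so the endpoint in section 2.12.1 keeps its meaning.

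V1 is optional. If it is used, state in advance whether it enters as a second covariate or through the mean of V1 and V2 as the single covariate. If the mean is chosen, name week-6 DHI as the outcome, because the equivalence with the change score then no longer holds. Day 0 alone is the safer default: its gain does not depend on how well V1 predicts week 6. The planned t-test or rank-sum test can stay as a sensitivity analysis.

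The change replaces the primary method and so needs a dated amendment. It needs no new data, visits or patients. Against the planned t-test it costs one degree of freedom with a single covariate and two with both.

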#### 2.12.2. Secondary Outcomes

The following outcomes will be evaluated at day 0, week 3, and week 6. The mean differences of scores for each scale (week 3–day 0; week 6–day 0) will be compared between the CMT and UC groups. Intragroup effects will also be explored for each outcome measurement.

*Mean Vertigo Score (MVS).* The MVS is a PRO assessing the intensity of dizziness [32–39], consisting of 12 items, each with 0 (none) to 4 (very strong) options. The score is the arithmetic mean of the total sum (range: 0–4).

*Visual Analog Scale (VAS). *The VAS will be measured as in previous studies of cervicogenic dizziness [2, 8, 9, 11–13] to rate the severity of dizziness. The zero end of the line represents “not dizzy at all,” whereas the other end (scored as 10 points) represents “the dizziest I can imagine being.”

*Dizziness Frequency. *Patients will be asked how many episodes of dizziness they experienced since the last assessment. The frequency will be scored as 0 (none), 1 (less than once per month), 2 (1–4 episodes per month), 3 (1–4 episodes per week), 4 (once per day), or 5 (twice or more per day), as in previous studies [11–13].

*Pain Intensity Numerical Rating Scale (PI-NRS). *The PI-NRS is an 11-point Likert scale that assesses the severity of neck pain perceived by a patient. This scale is widely used for pain studies [40], including neck pain [41]. A patient is asked to pick one value from 0 (not painful) to 10 (most painful) based on the pain level for the past 24 hours. Because cervicogenic dizziness often coincides with neck pain or stiffness, this scale has been included in this study.

*Neck Disability Index (NDI). *The NDI is a questionnaire that measures the level of disability of the cervical spine, including 0 to 5 points for each of 10 items: pain, personal care, lifting, reading, headaches, concentration, work, driving, sleeping, and recreation [42]. The final NDI score is interpreted as the level of disability (no, mild, moderate, severe, or complete disability). We plan to use a validated Korean version of the NDI in this study [43]. A recent clinical trial for cervicogenic dizziness also used the NDI for efficacy assessment [10].

*Cervical Range of Motion (CROM). *The CROM has been measured in many clinical studies of cervicogenic dizziness [2, 9–12]. Outcome assessors will evaluate the CROM for the cervical spine of a patient in flexion, extension, lateral bending, and rotation.

*Global Perceived Effect (GPE). *The GPE is a validated scale evaluating a patient's perception of symptom worsening or improvement after an intervention [44]. It consists of 7 options (1 for completely recovered to 7 for worst ever). Several studies of cervicogenic dizziness have used this assessment at the end of the intervention [2, 11–13].

*Korean Version of Perceived Stress Scale (K-PSS).* The K-PSS is the Korean version of the PSS, which measures the perceived level of stress for the previous 1 month [45]. It has 10 questions, and each can be answered with 1 (never), 2 (almost never), 3 (sometimes), 4 (fairly often), or 5 (very often).

*EuroQol Five-Dimension Questionnaire (EQ-5D). *The EQ-5D will be used to assess quality of life, consisting of two parts (EQ-5D-5L and EQ-VAS). EQ-5D-5L has 5 dimensions (mobility, self-care, usual activities, pain/discomfort, and anxiety/depression) and each dimension has 5 levels (no problems, slight problems, moderate problems, severe problems, and extreme problems) [46]. EQ-VAS rates a patient's health on a 20 cm vertical visual analog scale, with endpoints labelled “the best health you can imagine” and “the worst health you can imagine.” The EQ-5D has been translated into Korean and validated [47].

### 2.13. Blinding Assessment

This is an open-label study, but the outcome assessors will be blinded throughout. After the final assessment of each participant, the assessors will be asked which group they thought the patient belonged to: the CMT group, the UC group, or do not know. The blinding index (BI) will be calculated as described in Bang's study [23]. The index ranges from 1 (complete lack of blinding) to 0 (consistent with perfect blinding) to −1 (always guessed incorrectly). If the confidence interval (CI) of the estimated BI includes zero, the blinding will be considered successful.

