### 2.7. Randomization, Allocation, and Blinding

Random number sequences will be generated by an independent statistician ([name]) using SAS® 9.4 software (SAS Institute Inc., Cary, NC). The randomization will be block-stratified by the recruitment hospital to keep the numbers of each group similar throughout the study. The statistician will provide each hospital with sealed envelopes, in each of which a random number and an allocated group are written. Immediately after a participant is found to be eligible according to the screening process, a TKM doctor who will administer UC or CMT will open the next envelope in the sequence. Because this study is open-labeled to the investigators and patients, only the outcome assessors will be blinded. The outcome assessors will be TKM doctors different from those who administer CMT and UC. Only clinical emergency situations will allow breaking of the randomization code and blinding. At the end of the study, each outcome assessor will be asked which group he or she thought the patient was allocated to, and the answers will be used to calculate a blinding index (BI) [23].

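### A blinding-index interval that merely includes zero is taken as successful assessor blinding, although at 15 to 25 guesses per arm it often would be even with real unblinding

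*Protocol article*

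**What the plan says.** Section 2.13 of the protocol article asks for a guess after each participant's final assessment: "the assessors will be asked which group they thought the patient belonged to: the CMT group, the UC group, or do not know". Bang's blinding index is computed from the answers, on a scale where 1 is total unblinding and 0 is what perfect blinding would give. The decision rule follows: "If the confidence interval (CI) of the estimated BI includes zero, the blinding will be considered successful". The section gives no confidence level, no largest acceptable index and no precision requirement. It does not say whether one arm or both must pass.

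On who is blinded, section 2.7 is open: "Because this study is open-labeled to the investigators and patients, only the outcome assessors will be blinded". Section 2.12.1 states who rates the primary outcome: "The DHI is a patient-rated outcome (PRO) assessment". Section 2.12.2 names the outcome assessors as raters for one outcome, the cervical range of motion (CROM). Section 2.15 sets 25 participants per group and anticipates 40% drop-out.

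**The concern.** An interval that contains zero shows only that zero has not been ruled out. It may equally contain values that mean assessors usually knew the allocation. A rule that turns this into a positive verdict rewards imprecision, and this trial will be imprecise. It could therefore report successful blinding when assessors were guessing well above chance.

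The second matter is what the verdict covers. The index measures what assessors guessed, while patients who know their arm rate the DHI. Even an index of exactly zero would say nothing about reporting bias in the primary endpoint. The text around the rule does not state that limit, so a verdict of success printed beside a DHI result could be read too broadly.

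**Working it through.** The protocol gives no figure for the index, so there is none to reproduce. The check asks how often the rule would pass a given amount of true unblinding.

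**Inputs from the protocol article.** 25 per arm (section 2.15). With 40% drop-out, 25 x 0.6 = 15 per arm, if drop-outs contribute no guess. Three possible answers, including do not know (section 2.13).

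**Assumptions not in the documents.** A 95% Wald interval, the index calculated per arm, and a do-not-know share of 0%, 20% or 40%.

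**Formulas.** For one arm with n guesses:

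- BI = P(correct) - P(wrong)
- Var(BI) = [P(correct) + P(wrong) - BI^2] / n
- 95% interval = BI +/- 1.96 x sqrt(Var)

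**Step 1: width at an estimated index of 0.** The half-width is 1.96 x sqrt(share who guess / n).

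| n per arm | 0% do not know | 20% | 40% |
|---|---|---|---|
| 25 | 1.96 x sqrt(1/25) = 0.39 | 1.96 x sqrt(0.8/25) = 0.35 | 1.96 x sqrt(0.6/25) = 0.30 |
| 15 | 1.96 x sqrt(1/15) = 0.51 | 1.96 x sqrt(0.8/15) = 0.45 | 1.96 x sqrt(0.6/15) = 0.39 |

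Even a perfect estimate leaves an index of 0.30 to 0.51 unexcluded.

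**Step 2: results that pass.**

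- 17 correct and 8 wrong of 25: BI = 9/25 = 0.36. Var = (1 - 0.1296)/25 = 0.0348, SE = 0.187. The interval is 0.36 +/- 0.366, that is -0.006 to 0.73. It includes zero.
- 10 correct and 5 wrong of 15: BI = 0.33, interval -0.14 to 0.81. It includes zero.
- 9 correct, 3 wrong and 3 do not know of 15: BI = 0.40, interval -0.005 to 0.81. It includes zero.

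**Step 3: chance that one arm passes.** This was found by exact multinomial enumeration of all possible answer counts.

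| True BI | n = 25: 0% / 20% / 40% do not know | n = 15: 0% / 20% / 40% do not know |
|---|---|---|
| 0.2 | 85% / 77% / 72% | 77% / 83% / 79% |
| 0.3 | 69% / 56% / 45% | 65% / 70% / 61% |
| 0.4 | 49% / 32% / 18% | 48% / 52% / 37% |

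With no do-not-know answers, a true index of 0.3 means 65% correct guesses, since (1 + 0.3)/2 = 0.65.

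**Step 4: if both arms had to pass.** With independent arms and a true index of 0.3 in each, the one-arm probabilities are squared. At n = 25 this gives 48%, 31% and 20% for 0%, 20% and 40% do not know. At n = 15 it gives 42%, 48% and 37%.

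**The case against.** The strongest reply is that the index is a supporting check. No analysis set, sample size or hypothesis test depends on it. That stands, and it sets the weight of the point.

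The pass rates also depend on choices the protocol does not fix. At 25 per arm, do-not-know answers lower them, and a both-arms requirement lowers them at either size. This stands too, so the result is given as a range. The rule remains uninformative across that range.

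Four stronger readings are tempting, and the documents do not support them:

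- **That the plan uses the index to defend the DHI.** It does not. It calls the study open-label, says patients know their allocation and labels the DHI patient-rated. Assessor-blind is a fair description of the design. What can be said is only that the limit of the verdict is left unstated.
- **That assessor blinding matters for CROM alone.** CROM is the only outcome the text says assessors evaluate, but the article does not say who administers the questionnaires. An indirect influence of assessors on other outcomes cannot be excluded.
- **That fewer participants always make a pass easier.** With no do-not-know answers the reverse appears: at a true index of 0.3 the pass rate is 69% at 25 per arm and 65% at 15. The discreteness of the counts causes this. With 20% do not know, it rises from 56% to 70%.
- **That the timing of the guess is contradictory.** Section 2.7 says "At the end of the study, each outcome assessor will be asked which group", which can be read as the end of each patient's participation. Section 2.13 and Table 1 (visit 13) place the guess after each participant's final assessment.

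Finally, reporting by arm may already be part of the index method that section 2.13 cites. Saying so in the text would do no harm.

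**Conclusion.** The concern holds for the decision rule in section 2.13. As written, it converts a non-significant departure from zero into a finding of success. At a true index of 0.3 it would do so in one arm about 45% to 69% of the time with 25 guesses, and about 60% to 70% with 15. These figures rest on a 95% Wald interval per arm and a do-not-know share of 0% to 40%, neither of which the protocol states.

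The consequence is a possibly wrong statement about assessor blinding. The primary comparison is unaffected and severity is minor. A reader might infer that a failed or passed index changes how far the DHI result can be trusted. It does not in either direction, as far as patients' knowledge of their own allocation is concerned.

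**What to change.** In section 2.13:

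1. Delete the sentence that declares blinding successful.
2. State that the index will be reported for each arm with its confidence interval, and give the confidence level.
3. State that the result will be described as inconclusive where the interval is compatible with substantial unblinding.
4. Add that the index concerns the blinding of outcome assessors, chiefly relevant to the CROM they measure, and is not evidence against reporting bias in the DHI, which patients who know their allocation rate.

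The cost is a change of wording, with no new data and no change to the primary analysis. The downside is that the blinding result will probably be reported as inconclusive: even at an estimated index of 0, the upper limit is 0.30 to 0.39 with 25 per arm and 0.39 to 0.51 with 15.
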